##### Anthropometric assessments

Standardized procedures will be used to assess height and weight on all participating children and caregivers via calibrated stadiometers (Hopkins portable road rod stadiometer) and scales (BFHA-B400SV digital scale), respectively [31, 32]. Body mass index will be calculated using measured heights and weights. Centers for Disease Control and Prevention (CDC) age- and sex-adjusted BMI growth charts will be used to determine BMI z-scores for children to adjust for expected healthy growth and weight gain [31, 33]. Waist circumference will be measured on all participating children and caregivers with a tape measure at the uppermost lateral border of the hip crest (ilium) [31]. To adjust for expected growth among child participants, child WC z-scores will be determined using CDC age- and sex-specific growth charts [34].

##### Blood pressure

Blood pressure will be assessed on all participating children and caregivers via automated, calibrated BP monitors (Panasonic EW3109W). Age-, sex-, and height-adjusted National Heart, Lung, and Blood Institute (NHLBI) charts will be used to appropriately classify child BP [35].

##### Personal determinants

We will also assess immediate intervention targets relating to behavioral capabilities. For child participants, food preparation skills and frequency of involvement will be assessed at each data collection point by caregiver completion of an age-appropriate food preparation skills questionnaire designed to assess both skill ability and frequency of involvement in practicing the skill. Working from an existing validated questionnaire designed to assess child food preparation skills (ability) among 8–10 year olds [7], three versions of the questionnaire (4–5 year old questionnaire; 6–8 year old questionnaire; 9–10 year old questionnaire) were developed to accurately assess child food preparation skills (ability) according to age appropriateness. Assessment of frequency of involvement in practicing each food preparation skill was added to these modified questionnaires. The resulting questionnaires assessing a child’s ability to participate (8 items; 4-point scale; strongly agree to strongly disagree) and frequency of participation (8 items; 5-point scale; 0 times to 7+ times) in age-appropriate food preparation skills (during the past 30 days) included 16 items.

Among caregiver participants, menu planning skills and frequency will be assessed at each data collection point by caregiver completion of an existing menu planning questionnaire [36] to evaluate immediate intervention targets relating to behavioral capabilities. The 9-item menu planning questionnaire, which has demonstrated adequate internal consistency (α = 0.68) and high test-retest reliability (Pearson test-retest = 0.89), asks respondents to rate statements regarding menu planning, meal decision-making, and grocery shopping using a 4-point scale (‘never,’ ‘sometimes,’ ‘often,’ ‘always’).

A key affective variable - caregiver self-efficacy for healthy dietary practices related to family meals - will be assessed using an existing 12-item, 10-point scalar (0 = not at all confident; 10 = extremely confident) questionnaire [37]. The caregiver self-efficacy questionnaire, which will be completed by caregiver participants at each data collection point, has demonstrated high internal consistency (α = 0.88) among a sample of caregivers of 4–6 year old children. Tests of internal consistency will be run on all of the aforementioned questionnaires. Caregivers will also complete a brief food security questionnaire at each data collection point (6-item Short Form of the USDA Home Food Security Survey) [38] and a demographics questionnaire to assess key participant characteristics (age, race/ethnicity, education, employment, income) at baseline.

#### Home environment

##### Family meals

Weekly frequency of shared family dinners, shared family breakfasts, television viewing during family meals, and eating family meals in a dining area will be assessed via caregiver reports with 4, 5-point scalar (0 = never; 5 = 7 times) items from previous family meals research [39, 40].

### Process measures

Feasibility (program dose and fidelity) and acceptability will be assessed prospectively throughout the study as process outcomes. Program dose will be assessed by collecting weekly attendance (family and individual level) and tracking presence of caregiver/child dyads at each weekly lesson. Participants who demonstrate irregular attendance and/or discontinue participation will be contacted to learn underlying reasons for absence. To determine program fidelity, a trained observer will complete a program specific fidelity tool at the end of each weekly lesson, which will include a checklist of key program components, activities, and leader characteristics. Acceptability of the program will be measured with a caregiver-completed 5-item satisfaction survey administered at the end of the 10-week program [41]. At the end of programming, interviews will be conducted with a subset of caregivers to learn their perceptions of program strengths and weaknesses.

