### Study design

The study will be implemented over 12-months as a two-group (intervention; waitlist control) quasi-experimental trial using a staggered cohort design (Table 1). At each of three time periods, separated by 10 weeks, a cohort of 20 families will be recruited. Each cohort will be divided into an intervention and waitlist control group (10 families in each). Consequently, a total of 60 families (30 in the intervention group and 30 in the waitlist control group) will be enrolled. Upon confirmation of study eligibility, a baseline data collection appointment will be scheduled at the participating family’s home or the community center during the two weeks preceding intervention commencement. Data will be collected on the primary food preparing caregiver and all children 4–10 years old. Written caregiver consent and child assent will be obtained. Data will be collected on all outcomes via direct measure and questionnaires at baseline (time point 0, T0), 10-week post-test (time point 1, T1), and 10-week follow-up (time point 2, T2). Repeatability of the intervention (replication) will be evaluated by assessing measures on the waitlist control group at T1 and T2. Assessments will last up to 90 min. A team of trained research staff, blinded from group assignment, will facilitate data collection. Caregiver participants will receive a $25 grocery store gift card at each data collection point for their participation in the research. All study materials and procedures have been approved by the Institutional Review Board at Ohio State University.

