### Sample size and data analysis

Sample size was determined by examining the power of the test for comparing increases in frequency of family meals (day per week) of the intervention and waitlist control group. The data used to estimate power come from a previous pilot study, in which the main outcome of interest was the change in frequency of family dinners prepared and eaten at home together (weekly basis) from baseline to post-intervention [42]. Change in frequency of family dinners was used to power the current study because there is strong evidence that it has a downstream effect on the outcome of interest, child BMI [3, 42–44], and there are no previous studies that show a causal effect of family dinners on BMI. Based on these data, assuming 20% attrition [42], with an expected effect size of 0.7071, there will be 80% power to detect a difference in frequency of family dinners of 3 days per week with 30 families per group for a total sample size of 60 families at α = 0.05. Because the sample size in the previous pilot study was small and uncertainty about estimated effect size was large, we used a conservative estimate of effect size (i.e., the lower bound of a 95% confidence interval) for the power calculation.

Data from each of the three cohorts will be pooled and the intervention tested by comparing change (T1-T0) in diet quality, anthropometric measures, and blood pressure of child and caregiver participants in the intervention compared to participants in the waitlist control (hypotheses 1.1 and 2.1). Multiple regression models will be used to determine the association between the difference in the response variables of interest between the intervention and control group, controlling for potential confounders (race/ethnicity, income, cohort, intervention dose), from baseline (T0) to 10-week post-test(T1) and 10-week follow-up (T2). For families in which data will be collected on multiple children, the effect of family will also be controlled by including a random effect for family.

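### The satisfaction survey comes only at the end of the programme, so families lost before then have no stated route into the acceptability result

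*Protocol article*

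**What the plan says.** The Process measures section of the protocol article opens with "Feasibility (program dose and fidelity) and acceptability will be assessed prospectively throughout the study as process outcomes". Dose is then tracked through weekly attendance of families and individuals, and fidelity through an observer's checklist after each lesson.

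Acceptability has one scored instrument, a "caregiver-completed 5-item satisfaction survey administered at the end of the 10-week program". A second, qualitative source is placed at the same time: "At the end of programming, interviews will be conducted with a subset of caregivers to learn their perceptions of program strengths and weaknesses".

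Families who drift away are covered by one sentence, which sits with the text on programme dose: "Participants who demonstrate irregular attendance and/or discontinue participation will be contacted to learn underlying reasons for absence".

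The Sample size and data analysis section sets the study size "assuming 20% attrition". The Study design section schedules assessments at baseline (T0), after 10 weeks (T1) and 10 weeks later (T2), with a gift card for the caregiver at each one.

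**The concern.** Acceptability asks whether the programme suits the families it was made for. Families who stop coming are the ones whose opinion is most informative on that question, and they are the hardest to reach at the final week. The article collects the rating only then. It does plan to reach these families earlier, but with a different question, namely why they were absent.

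What is at stake is how a satisfaction score can be read. The Discussion expects difficulty in engaging this population and gaining its trust, and the abstract says the results are meant to guide practitioners. A score that rests mainly on families who stayed would say less about the programme's fit for underserved families than its label suggests.

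**Working it through.** The article gives no acceptability target, expected score or response rate, so there is no stated figure to reproduce. The check has two parts: who can be rated under the text, and how much a gap could matter.

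**Routes into the acceptability result**

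- *Family that attends to the end.* It can answer the survey.
- *Family that stops lessons but stays in the study.* It can be reached at T1 (T2 for the waitlist group), which falls at the end of its programme period. The article does not say that the survey is given at that visit. If it is handed out at the last lesson, this family is missed.
- *Family lost to the study before the end of the programme.* It is missed under either arrangement. The remaining contact asks for reasons, not for the five ratings.

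**Count**

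Inputs: 20% attrition (Sample size and data analysis) and 30 intervention families (Study design). 0.20 × 30 = 6 families. This assumes that attrition is equal in the two groups. The 20% is study attrition; the share that stops lessons may differ and is not given.

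**Size of a possible bias**

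Let *a* be the share of starters who leave, *r* the share of leavers not surveyed, *S* the mean score of stayers and *D* the stayer-minus-leaver difference in mean score. Assume that all stayers answer.

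- Mean over all starters: S − a·D
- Mean over respondents: S − D·a(1 − r)/(1 − a·r)
- Bias (respondents minus all starters): D·[a − a(1 − r)/(1 − a·r)]

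With a = 0.20:

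| r | Bias |
|---|---|
| 0 | 0 |
| 0.25 | 0.042 × D |
| 0.50 | 0.089 × D |
| 0.75 | 0.141 × D |
| 1 | 0.200 × D |

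If all leavers are missed, D = 0.5 points gives 0.10 points and D = 1 point gives 0.20 points. If D = 0 there is no bias whatever r is. Both r and D are assumptions; the article supplies neither.

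**The same result as a percentage, for illustration only**

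The article does not say that the survey will be summarised as a percentage satisfied. Suppose it is, that 95% of stayers are satisfied and that no leaver is surveyed:

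- Leavers 40% satisfied: 0.8 × 95% + 0.2 × 40% = 76% + 8% = 84%. The reported 95% is 11 points too high, which equals 0.20 × (95 − 40).
- Leavers 0% satisfied: 0.8 × 95% = 76%, so 19 points too high.
- Leavers 80% satisfied: 76% + 16% = 92%, so 3 points too high.

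**The case against.** The best reply is that a time point is not an eligibility rule. The article says when the survey is given and does not restrict it to families still attending. T1 and T2 do not depend on lesson attendance and carry an incentive, so a family that stopped lessons may well be surveyed. The interview subset has no selection rule and could include families who stopped. Weekly attendance will be visible beside any score, and reasons for leaving will be collected. This is also a condensed article, and acceptability is neither a main outcome nor part of any hypothesis.

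Most of this stands, and it rules out several stronger readings that a reader might infer:

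- *That families who stop are excluded from the survey.* No such rule is written.
- *That the result is biased upward.* This needs leavers to be both unsurveyed and less satisfied. The article establishes neither, and it names scheduling conflicts as a feature of these families, so stopping need not mean dissatisfaction.
- *That 12 of 60 families would go unrated.* Applying 20% to all 60 mixes study attrition with programme starters. Waitlist families lost before their first lesson never started and could not rate the programme.
- *That end-of-programme timing contradicts the opening sentence on assessment throughout the study.* With three staggered cohorts, programme ends recur during the study, so the two statements can be reconciled.

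What the reply does not answer is the family lost to the study before the end. For that family the article does fix something: the survey's timing, and a contact whose stated purpose is narrower than the survey. Giving a reason for absence is not the same as giving a rating, and nothing written turns one into the other.

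**Conclusion.** The point holds in a limited form. As written, families lost before the programme ends have no stated route into the acceptability score. They would number about 6 of 30 intervention families if the assumed study attrition applies equally. The score may be too favourable if leavers are less satisfied, by at most 0.20 × D at 20% loss, and by less to the extent that some leavers are reached. Neither the direction nor the size can be derived from the article.

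This is a cheap improvement of low priority. The measure is descriptive, and no main outcome, test or decision depends on it.

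**What to change.** In the Process measures section:

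- Offer the same five items to every caregiver who started the programme. For irregular attenders and discontinuers, ask them at the contact already planned to learn reasons for absence.
- Report acceptability over all starters, with the response rate, as well as over completers.
- Optionally, state that the interview subset may include some families who stopped.

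The cost is five extra questions in a contact that will take place anyway, and one more line in the results. There are two downsides. Some discontinuers will not answer, so the all-starter figure will still be incomplete, which is why the response rate is needed. Answers given at that contact may also differ somewhat from those on the end-of-programme survey because of the mode of asking.

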### Sample size and data analysis

Sample size was determined by examining the power of the test for comparing increases in frequency of family meals (day per week) of the intervention and waitlist control group. The data used to estimate power come from a previous pilot study, in which the main outcome of interest was the change in frequency of family dinners prepared and eaten at home together (weekly basis) from baseline to post-intervention [42]. Change in frequency of family dinners was used to power the current study because there is strong evidence that it has a downstream effect on the outcome of interest, child BMI [3, 42–44], and there are no previous studies that show a causal effect of family dinners on BMI. Based on these data, assuming 20% attrition [42], with an expected effect size of 0.7071, there will be 80% power to detect a difference in frequency of family dinners of 3 days per week with 30 families per group for a total sample size of 60 families at α = 0.05. Because the sample size in the previous pilot study was small and uncertainty about estimated effect size was large, we used a conservative estimate of effect size (i.e., the lower bound of a 95% confidence interval) for the power calculation.

Data from each of the three cohorts will be pooled and the intervention tested by comparing change (T1-T0) in diet quality, anthropometric measures, and blood pressure of child and caregiver participants in the intervention compared to participants in the waitlist control (hypotheses 1.1 and 2.1). Multiple regression models will be used to determine the association between the difference in the response variables of interest between the intervention and control group, controlling for potential confounders (race/ethnicity, income, cohort, intervention dose), from baseline (T0) to 10-week post-test(T1) and 10-week follow-up (T2). For families in which data will be collected on multiple children, the effect of family will also be controlled by including a random effect for family.

Sustainability of intervention effects will be tested by pooling intervention group data from each of the three cohorts, comparing change (T2-T1) in diet quality, anthropometric measures, and blood pressure among intervention group participants at the end of the 10-week follow-up period (hypothesis 1.2 and 2.2). Intervention replication will be assessed by pooling waitlist control group data from each of the three cohorts, comparing post-program change in diet quality, anthropometric measures, and blood pressure among waitlist control participants (T2-T1) to intervention participants (T1-T0). Significance will be set at *p* < 0.05.

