## Methods

### Objectives and hypotheses

The objectives of this study with related hypotheses will be as follows:Assess the impact of Simple Suppers on children and caregivers of participating families relative to children and caregivers of families in the control group.Hypothesis 1.1.Diet quality, BMI z-scores and BMI, waist circumference (WC) z-scores and WC, and BP z-scores and BP will improve more from baseline to post-intervention among children and caregivers, respectively, participating in the intervention than in the controls.Hypothesis 1.2.Diet quality, BMI z-scores and BMI, WC z-scores and WC, and BP z-scores and BP improvements will be maintained during the follow-up period among children and caregivers, respectively, participating in the intervention.

Objective 2.Assess the impact of Simple Suppers on the family meals environment of participating families relative to the controls.Hypothesis 2.1.Frequency of family meals (breakfast and dinner), TV viewing during meals, and eating family meals in a dining area will improve more from baseline to post-intervention among families participating in the intervention than in the controls.Hypothesis 2.2.Frequency of family meals (breakfast and dinner), TV viewing during the meals, and eating family meals in a dining area improvements will be maintained during the follow-up period among families participating in the intervention.

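### The 80% power claim does not state sidedness: with 24 completers per group it is about 67% two-sided, and is approached only by an undeclared one-sided test

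*Protocol article*

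**What the plan says.** The sample-size justification is in the Protocol article, Sample size and data analysis. It is based on the change in weekly family dinners from baseline to post-intervention, compared between the intervention and waitlist groups. It states "with an expected effect size of 0.7071, there will be 80% power to detect a difference in frequency of family dinners of 3 days", where the difference is a weekly count. The sample is given as "with 30 families per group for a total sample size of 60 families at α = 0.05". It assumes 20% attrition and describes the effect size as the lower limit of a 95% confidence interval from a small pilot. The SD is not given.

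Study design makes clear that 60 families, 30 per group, is the number enrolled and not the number expected to complete.

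No section says whether the test is one-sided or two-sided. The analysis text closes with "Significance will be set at *p* < 0.05", and the Abstract gives the same threshold without qualification. The hypotheses are directional: family-meal measures "will improve more from baseline to post-intervention among families participating in the intervention than in the controls".

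**The concern.** A significance level of 0.05 with nothing further said is normally read as two-sided. On that reading, 24 completers per group at an effect size of 0.7071 do not give 80% power. A reader who takes the sentence at face value would put the chance of missing the planned effect at about 1 in 5, when on the two-sided reading it is about 1 in 3. This is the article's only sample-size justification, so the figure affects how much weight a non-significant result on family dinners can bear.

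**Working it through.** **Inputs** (Sample size and data analysis, unless noted)
- Standardised effect d = 0.7071, read as the between-group difference in change divided by its SD
- Raw difference 3 days per week
- α = 0.05, sidedness not stated
- 30 families enrolled per group (enrolment confirmed in Study design)
- Attrition 20%, taken as equal in both groups, so 30 × 0.8 = 24 completers per group

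**Formula.** For n per group, the noncentrality is d × √(n/2). The normal-approximation power is Φ(d√(n/2) − z), with z = 1.960 two-sided and 1.645 one-sided. The noncentral t version uses 2n − 2 degrees of freedom.

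**Step 1: can the stated 80% be reproduced?** With n = 24, the noncentrality is 0.7071 × √12 = 2.449.
- Two-sided: Φ(2.449 − 1.960) = Φ(0.489) = 68.8%
- One-sided: Φ(2.449 − 1.645) = Φ(0.804) = 79.0%

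The same calculation for other n, with the noncentral t results:

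| Completers per group | Two-sided, t | Two-sided, normal | One-sided, t | One-sided, normal |
|---|---|---|---|---|
| 24 (20% attrition) | 66.9% | 68.8% | 77.9% | 79.0% |
| 25 | 68.8% | 70.5% | 79.4% | 80.4% |
| 30 (no attrition) | 76.8% | 78.2% | 85.6% | 86.3% |

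No two-sided entry reaches 80%, even with attrition ignored. With the stated attrition, only the one-sided test comes near.

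**Step 2: where could 30 per group come from?** The normal-approximation requirement is n = 2(z + 0.8416)²/d², with d² = 0.5.
- Two-sided: 2 × (1.960 + 0.8416)²/0.5 = 31.4, so 32 completers per group (33 by t)
- One-sided: 2 × (1.645 + 0.8416)²/0.5 = 24.7, so 25 completers per group (26 by t)

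The one-sided 25 multiplied by 1.2 is exactly 30. But if 20% of those enrolled are lost, the number to enrol is 25/0.8 = 31.25, so 32. This reconstruction fits the stated figure but is an inference.

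**Step 3: what can 24 completers per group detect with 80% power?**
- Two-sided: 0.826 SD by t; by normal approximation (1.960 + 0.8416) × √(2/24) = 0.809 SD
- One-sided: 0.729 SD by t; 0.718 SD by normal approximation

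**Step 4: the link to days.** The two stated figures imply an SD of change of 3/0.7071 = 4.24 days. If that is the SD used, the detectable differences (t) are 0.826 × 4.24 = 3.50 days two-sided and 0.729 × 4.24 = 3.09 days one-sided.

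**The case against.** The strongest reply is that the article never says two-sided. Its hypotheses are directional, a one-sided 5% calculation at 24 completers gives 78–79%, and 25 × 1.2 gives exactly the stated 30. A condensed article may also leave sidedness to the full protocol or analysis plan. This reply stands in part. A reader might infer that the 80% is simply false, but the documents do not support that flat statement, because a one-sided test nearly reproduces it. The reply does not clear the sentence, however. Directional hypotheses are usual in two-sided trials and do not declare a one-sided test. The choice moves power by about 11 points (77.9% against 66.9%, t). Even one-sided, 80% is not quite reached at 24 completers.

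A reader might also infer that 3 days and 0.7071 contradict each other, because an SD of 4.24 looks too large for a count of 0 to 7 days. The documents do not show this. The powered quantity is a change score, which can run from −7 to +7. In addition, 3/(3√2) = 0.7071, so an SD of 3 at each time point with uncorrelated measurements would give exactly this pair. A larger SD also makes the standardised effect smaller, which is the conservative direction. What remains is that the SD is not stated.

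Two further points temper the consequence. The 0.7071 is itself described as a conservative lower limit, so the 1-in-3 risk applies at that effect and would be smaller if the true effect is larger. The planned analysis is covariate-adjusted regression, which could raise power. Dividing d by √(1 − r²), an assumed covariate–outcome correlation r of 0, 0.3 or 0.5 gives 66.9%, 71.0% or 79.1% two-sided at 24 per group (t). The article gives no such correlation and does not rely on one.

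**Conclusion.** The point holds as a defect in the power statement. With the stated effect size, enrolment and attrition, power is about 67% (t) or 69% (normal) if the 5% test is two-sided, which is 11 to 13 points below the stated 80%. If the test is one-sided, power is 78–79%, close to the claim, but that test is not declared. The best available reconstruction of the 30 per group applies the 20% attrition by multiplication where division is needed.

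This rests on three assumptions: 0.7071 is a standardised mean difference, attrition is equal in the two groups, and the comparison is an unadjusted family-level comparison of change. It does not show that the study is badly sized for the effect the authors truly expect, or that the 3-day figure is wrong.

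**What to change.** In Sample size and data analysis:
- State whether the 5% test is one-sided or two-sided.
- Restate the power for 24 completers per group (48 of 60 families). If two-sided, report about 67% at an effect size of 0.7071, with 0.83 SD as the effect detectable at 80% power. If one-sided was intended, declare it and report about 78%.
- Say how attrition was applied.
- Give the SD of change that connects 0.7071 to 3 days (4.24 days if both figures stand), and quote the detectable difference in days from that SD.

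This is a change of wording. It needs no extra enrolment and no change to the analysis. The only downside is that the stated power becomes less favourable.

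### The 80% power figure gives no sidedness; with 20% attrition a conventional two-sided 5% test has about 67% power, and only an unstated one-sided test comes near 80%

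*Protocol article*

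**What the plan says.** All of the sizing is in one paragraph of the protocol article, under Sample size and data analysis. The test being powered is the one for "comparing increases in frequency of family meals (day per week) of the intervention and waitlist control group". The inputs are given as "assuming 20% attrition [42], with an expected effect size of 0.7071", and the result is that "there will be 80% power to detect a difference in frequency of family dinners of 3 days per week with 30 families per group", with alpha set at 0.05. The same paragraph calls the effect size conservative, because it is the lower limit of a 95% confidence interval from a small pilot.

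The Study design section fixes what the 30 per group means: "a total of 60 families (30 in the intervention group and 30 in the waitlist control group) will be enrolled". So 30 is the number before losses.

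On sidedness the article is silent. The power statement gives only the alpha level. The analysis text plans multiple regression with significance at p < 0.05. Hypothesis 2.1, under Objectives and hypotheses, is worded in one direction (more improvement with the intervention), but it does not specify a test.

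**The concern.** Power for comparing two means depends on the effect size, the number analysed per group, alpha and the number of sides. The article gives the first three and omits the fourth. Under the usual default, two-sided, the stated 80% is not reached once the plan's own attrition is applied.

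This is the only power statement in the article, on the only outcome used for sizing. If the true figure is nearer two in three than four in five, a non-significant result for family dinners would be read as stronger evidence against the programme than the design can supply.

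**Working it through.** **Inputs.** Effect size d = 0.7071, read as a standardised mean difference (the type is not stated); alpha 0.05; 20% attrition; 30 enrolled per group. Analysable families: 30 × 0.8 = 24 per group.

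**Formula.** Noncentrality = d × √(n/2), with n per group. By the normal approximation, power = Φ(noncentrality − z), with z = 1.960 two-sided or 1.645 one-sided. The exact version uses the noncentral t with 2n − 2 degrees of freedom.

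- n = 24: 0.7071 × √12 = 2.449
- n = 30: 0.7071 × √15 = 2.739

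**Trying to reproduce 80%.**

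| Analysed per group | Test at 5% | Normal | t |
|---|---|---|---|
| 24 (20% attrition) | two-sided | 68.8% | 66.9% |
| 30 (no attrition) | two-sided | 78.2% | 76.8% |
| 24 (20% attrition) | one-sided | 79% (0.7895) | 77.9% |
| 30 (no attrition) | one-sided | 86.3% | 85.6% |

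With attrition included, only the one-sided row comes near 80%.

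**Working back from 80%.** By the normal formula, n = 2(z + 0.842)²/d².

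- One-sided: 2 × (1.645 + 0.842)²/0.5 = 24.7, so 25 per group (26 by the t test). Power at 25 is 80.4% (normal) or 79.4% (t). Multiplying 25 by 1.2 gives exactly 30, a plausible origin of the stated size. But 20% lost from 30 leaves 24, not 25. The inflation that allows for a 20% loss is 25/0.8 = 31.25, so 32.
- Two-sided: 2 × (1.960 + 0.842)²/0.5 = 31.4, so 32 per group (33 by the t test). Enrolment would be 32/0.8 = 40, or 33/0.8 = 41.25, so 42 per group.

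**Detectable effect at two-sided 80% power (t test).** 0.826 with 24 per group; 0.736 with 30 per group.

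**Other meanings of 0.7071.** If the difference had been divided by SD × √2, then d = 1.0 and two-sided power at 24 per group is 92%. If 0.7071 were Cohen's f, power exceeds 99%. Neither gives 80%.

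**The case against.** The strongest defence is that the figure was derived one-sided. The hypotheses are directional, no section says two-sided, and 25 × 1.2 = 30 matches the stated size exactly. On that reading the gap is 1 to 2 percentage points, which is close to rounding. This stands as a plausible account of how the number arose. It does not settle the matter, because a directional hypothesis is not a one-sided test, p-values for regression coefficients are two-sided by convention, and a one-sided sizing followed by a two-sided analysis would still have 67% to 69% power.

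The defence also notes that 0.7071 is a deliberately low value, so power at the pilot's point estimate would be higher. That is true, by an amount the article does not show. But 80% is claimed at 0.7071 itself, so this margin does not make a two-sided claim correct.

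Sidedness may also be given in a full protocol or analysis plan that is not shown. The silence alone is therefore not the point. The point is a printed figure that holds, approximately, under only one unstated choice.

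A reader might go further and infer that 80% contradicts the plan's inputs on every reading, or that an arithmetic error is proven. The article does not support that. Two-sided testing is an assumption brought to it, and the one-sided reading comes within about 2 points. Nor is the two-sided figure without attrition strong evidence by itself, since 78.2% by the normal approximation is under 2 points from 80%.

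**Conclusion.** The point holds conditionally. If the dinner-frequency comparison is tested two-sided at 5%, power at the assumed effect with the assumed attrition is about 67% (t) to 69% (normal), not 80%. By the t test the type II error is about 33% instead of 20%. If a one-sided 5% test was intended, power is 78% to 79% and the statement is only slightly generous, but the article must then say so.

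This rests on reading 0.7071 as a standardised mean difference, on 30 per group being the enrolled number, as the Study design section says, and on 20% loss in each group. It does not depend on the standard deviation behind the three-day difference. It concerns family dinner frequency only; the article makes no power claim for child diet quality or BMI z-score.

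**What to change.** Keep the 60 families, state the sidedness that the analysis will use, and restate the power to match.

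- If two-sided: *With 60 families enrolled and 20% attrition (24 per group analysed), power is about 67% for an effect size of 0.7071; 80% power is reached at an effect size of about 0.83.*
- If one-sided 5% was intended: say so, and report about 78% for 24 analysed per group.

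In either case, commit to interpreting a non-significant dinner-frequency result through its confidence interval.

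The cost is a corrected power statement and a less favourable figure. No further families are needed, and design and conduct do not change.
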